## Abstract

**Background:**

Down syndrome is the most common cause of learning disability, affecting approximately 1 in every 700 babies. Children with Down syndrome have particular difficulties with speech and language. This makes it challenging for them to participate fully in life, access healthcare services and educational opportunities. Improving the language skills of young children with Down syndrome is vital for their future social and emotional well-being and behaviour, and consequently contribution to society. As Down syndrome is detected before or at birth, we can provide support from early on. There are currently no standard interventions for improving the language skills of children with Down syndrome under the age of 36 months. Evidence suggests that early parent-based interventions may be effective in improving language outcomes. In partnership with parents and speech and language therapists, we have co-developed an intervention focusing on early social communication skills and our preliminary work shows that it can lead to better language in children with Down syndrome. Our aim is to carry out a feasibility study which will inform a future pilot/full trial to test whether the intervention is effective in improving language skills before children with Down syndrome start school.

**Methods:**

This is a two-arm feasibility randomised controlled trial (RCT), with 1:1 randomisation stratified by trial site comparing the intervention (plus standard NHS speech and language therapy) with no intervention (standard NHS speech and language therapy only). We aim to recruit between 25 and 30 children with Down syndrome aged between 11 and 36 months. Sites are defined by the geographical boundaries of three National Health Service (NHS) Trusts. Recruitment is from NHS Speech and Language Therapist caseloads within the 3 Trusts, and self-referral. In the intervention arm, parents/guardians will receive brief training on the parent-based intervention and a manual to follow with their child for 10 weeks. The children’s language and early communication skills and family health outcomes will be assessed by a blinded assessor at baseline, post-intervention and 6 month follow-up. Questionnaire and semi-structured interviews will explore the acceptability of the intervention to parents and SLTs.

**Discussion:**

The feasibility study’s outcomes will determine whether it would be viable to progress to a full-trial and whether adjustments need to made to the procedures, data collection methods, intervention delivery and the intensity of support needed. We want to assess whether our early intervention can be delivered and rolled out through NHS Speech and Language Therapy (SLT) Services. We anticipate that NHS SLT Services will need to make ongoing changes due to the COVID-19 pandemic, so it is likely that we will need to make adjustments for the definitive trial. We will also calculate descriptive statistics of the language outcome measure which we will use for any future sample size calculation.

**Trial registration:**

ISRCTN13902755. Registered on 25 August 2020. http://www.isrctn.com/ISRCTN13902755

## Background and rationale

### Clinical need

Down syndrome is a genetic condition which affects 1 in 700 live births [1] and is the most common cause of learning disability [2]. There are approximately 38,000 people with Down syndrome living in England and Wales [3]. Language is a particular weakness in this population, and it can even be lower than expected for the level of cognitive functioning. Children with Down syndrome acquire language slowly and often there are severe delays. Some children with Down syndrome enter school with a spoken vocabulary of approximately 300 words [4] compared to typically developing children who have thousands of words [5]. Because language ability at school entry is a predictor of later psycho-social and academic outcomes [6], and early language skills are a primary child well-being indicator [7], it is crucial that children with Down syndrome have as good as possible early language skills, to optimise health and well-being outcomes of both children and their parents. Having a child with Down syndrome can affect parental stress levels and mental health. The stress levels of mothers of children with Down syndrome increases as their child gets older, possibly due to difficulties in accessing services and worrying about their child’s future [8].

Language and communication skills are strongly linked to health outcomes including quality of life, mental health and well-being and access to healthcare. For example, the recommendation to prioritise early language skills as a child well-being indicator was first made by the Equality and Human Rights Commission [9]. Interventions to support language and communication development have been identified by James Lind Alliance Priority Setting Partnership for Childhood Disability [10]. Importantly, the Early Intervention Foundation has recently issued a call to prioritise early language skills as a primary child well-being indicator [7].

Being able to communicate effectively is a critical factor for living safely and independently in the community, and in obtaining the highest quality healthcare [11]. In the twenty-first century, a person’s fitness for survival is determined in terms of their ability to communicate effectively [12]. People with communication disabilities are at risk of not being able to communicate effectively with their healthcare providers, which may directly compromise their health, the healthcare they receive and their right to fully participate in decisions regarding their health [13]. Poor language and communication in childhood has also been linked to poorer long-term outcomes in terms of communication skills, occupational status and educational outcomes [14].

The aim of this project is to empower parents to be able to feel confident in promoting and facilitating their children’s language and communication development from an early age. The Council for Disabled Children emphasises the importance of empowering parents [15]. Improving the language skills of children with Down syndrome in the pre-school years will mean improved quality of life for both children and parents, better health outcomes, reduced parental stress levels and better social and educational participation.

Well-designed interventions focusing on the foundation skills for language are needed to improve language outcomes for children with Down syndrome. Early intervention can be effective, and there is evidence for the effectiveness of early intervention from clinical populations, including children with language delay and autism spectrum disorders [16, 17]. Evidence suggests that the earlier an intervention is delivered, the better the language outcomes [16]. We conducted a systematic review of early interventions for children with Down syndrome under 6 years of age and identified 11 studies involving 242 children, which were either described as RCTs, or included a control group, and had speech/language/communication as primary outcome measure. Although most intervention studies showed positive effects of the interventions on children’s speech and language outcomes, they are hampered by methodological issues and risk of bias [18].

This protocol describes the methods and analysis for a two-arm randomised feasibility trial that will compare the intervention (in addition to standard NHS speech and language therapy) with no intervention (standard NHS speech and language therapy only). The aim is to investigate the acceptability of the intervention and feasibility of a randomised controlled trial and bridge a gap in the current evidence-base for early social communication interventions for children with Down syndrome under the age of 3.

### Early social communication skills as precursors to language

Language development happens in the social context and early social communication skills (before children produce words) are crucial [19–21] and lay the foundation for language to be acquired. A subset of early social communication skills includes, for example, shared attention skills, which is the focus of this research. Shared attention is when the child and parent/caregiver simultaneously focus on the same object or event (for example, both parent and child are looking at a toy simultaneously). If it is the child who chooses an object or topic/event upon which the attention of the child and caregiver is focused, we say that the child has initiated shared attention. When the parent/caregiver chooses a toy/topic to which the infant’s attention is directed, such as for example, the parent points to a toy to get their child’s attention and the child looks at that toy, the child is responding to shared attention. The child’s responding to bids of shared attention results in getting verbal responses from caregivers, which in turn increases the language input the child receives [22] and good quality and quantity of input is crucial in supporting children’s language acquisition [23–26].

Importantly, how well the child responds to the parent/caregiver’s bids for shared attention has been found to be a unique predictor of later language outcomes in children with Down syndrome [20, 27]. Preliminary work by our research team shows that responding to shared attention at 18‑21 months uniquely predicts expressive language outcomes at 32‑35 months in infants with Down syndrome [27]. This finding is based on a longitudinal investigation including 14 children with Down syndrome (aged 18 to 21 months at the start of the study) and 35 typically developing children (matched on non-verbal abilities to the Down syndrome group). All children were seen at 3 time points over 14 months. Interestingly, in typically developing children, speech segmentation skills (and not responding to shared attention) emerged as the longitudinal predictor of language. This difference between children with Down syndrome and the typical children suggests that early social communication skills, and specifically the child’s responding to shared attention, are very important for language development in children with Down syndrome, and an intervention targeting these skills may lead to better language outcomes.

To address this, we have developed an early social communication intervention focused on shared attention. Our preliminary work showed that it can lead to better language in children with Down syndrome [28]. Following this preliminary work, we co-developed a parent-led intervention in collaboration with parents of children with Down syndrome and speech and language therapists designed to be delivered by parents, with the support of brief training and ongoing advice provided by NHS speech and language therapists over 10 weeks.

#### Aims and objectives

The *aim* of this feasibility study is to estimate the parameters to inform a future randomised controlled trial that will evaluate whether the intervention plus standard care is more effective than standard care for enhancing the language and early communication skills and family health outcomes for children with Down syndrome. We want to assess whether our early intervention can be delivered and rolled out through NHS Speech and Language Therapy Services.

The *objectives* are as follows:Determine whether parents of children with Down syndrome are willing to be randomisedDetermine the acceptability of the intervention to speech and language therapists and effectiveness of recruitment of children with Down syndrome by speech and language therapistsIdentify different routes to identifying eligible children with Down syndrome (paediatricians, health visitors, speech and language therapists, charities)Estimate follow-up rate and adherence to interventionInform the measurement of health economic outcomes and resource implications of a parent-led interventionDetermine the standard deviation of the primary outcome measure to inform a sample size calculation for a full trial

The effectiveness of the intervention will not be determined in this feasibility study but will be the aim of a subsequent full trial. The feasibility study’s outcomes will determine whether it would be viable to progress to a full-trial and whether adjustments need to made to the procedures, data collection methods, intervention delivery and the intensity of support needed. We anticipate that NHS services will need to make ongoing changes due to the COVID-19 pandemic, so it is likely we will need to make adjustments for the definitive trial.

### Trial design

This study is a two-arm randomised feasibility trial that will compare the intervention (in addition to standard NHS speech and language therapy) with no intervention (standard NHS speech and language therapy only) across three NHS sites. The intervention will be delivered by parents with the support of brief training and ongoing advice provided by NHS speech and language therapists over 10 weeks. The protocol has been developed in line with the Standard Protocol Items: Recommendations for Interventional Trials (SPIRIT) 2013 Checklist. See Fig. 1 for a flowchart of the study.

**Fig. 1 Fig1:**
[figure not shown]
Flow diagram

### Setting

The study will be conducted in 3 NHS sites in England, providing Speech and Language services across three geographical regions: Berkshire Health NHS Foundation Trust (BHFT), Oxford Health NHS Trust (OHFT) and North East London Foundation Trust (NELFT) (http://www.isrctn.com/ISRCTN13902755). All assessments will be conducted remotely using either online or paper questionnaires, with support by telephone. The study is being led by the University of Reading and the lead R&D organisation is BHFT.

### Participants

#### Sample size

Between 25 and 30 children with Down syndrome aged between 11 and 36 months old will be enrolled in this feasibility study over a period of between 6 and 10 months. Given the feasibility nature of the study, no formal sample size calculations were performed; however, the literature recommends a minimum of 24 participants [29–31] in order to derive a standard deviation.

### Eligibility criteria

#### Inclusion criteria

Parent or guardian willing and able to provide informed consent on behalf of participant.Confirmed diagnosis of trisomy 21 (Down syndrome).Male or female child, 11 to 36 months old at study entry.Parent/guardian has the literary and language skills needed to use intervention manual.The participant has not previously been entered into this study.The child is not currently taking part or planning to take part in a language-based intervention study.

#### Exclusion criteria

Children with co-morbid conditions (for example Down syndrome and Autism spectrum disorder) as determined by the Principle Investigator.Any reason in the opinion of the Principal Investigator that the child is not suitable for study participation.Prior knowledge of the intervention as specified in the parent manual.

### Intervention

The intervention focuses on promoting the development of early social communication skills and in particular, the child’s ability to respond to shared attention. The parent/guardian will be provided with an intervention manual (paper based), a bag of age-appropriate toys and links to short video demonstrations of the intervention, with explanation from either the PI or the child’s speech and language therapist. The intervention will be administered in the child’s home by the parent/guardian. The parent/guardian will be advised to progress through the stages of the intervention step by step and practise 3‑6 times a week, totaling an hour a week, for 10 weeks. Support to deliver the intervention from the child’s speech and language therapist (SLT) (all of whom have had training on how the intervention works) will be available at the request of parents by telephone/email. Parents also have access to the PI of each site. The SLT will record all contacts from parents in the child’s case notes including duration and content of each contact. There will be two telephone calls from the PI, one at week 4 and the second at week 8 to offer support and check and ensure adherence to the intervention manual. They will ask a standard set of questions including how closely parents are following the manual, how often they do the intervention and for how long.

The participants in the intervention group will continue to also receive their usual care.

#### Comparator

The comparator is standard NHS speech and language therapy for this patient group.

### Procedure

Speech and language therapists from participating NHS Trusts will identify potential participants (children with Down syndrome) and their parents by reviewing their caseloads against the inclusion criteria. We will also publicise the study via other healthcare professionals and charities to give other potential participants the opportunity to self-refer to take part in the study.

The speech and language therapists (standard care team) will introduce the study to the parents of all potentially eligible children at a routine appointment, or will contact parents specifically to introduce the study, and ask them if they may be interested in taking part. The parent will be provided with a participant information sheet giving details of what study participation will involve and asked to contact the research team if they may be interested in taking part, or if they have questions.

Parents will have as long as they need to consider participation and the opportunity to ask the speech and language therapist, the research team or other health professionals as many questions as they like in order to make their decision. Parents may choose to delay study entry to fit in with other family commitments. Where possible, reasons will be gathered if a family chooses not to participate by the child’s speech and language therapist.

Self-referring participants will receive the same information and have the same opportunities to discuss the study with members of the research team and ask any questions before they decide whether they would like to take part. If they do not currently have an NHS speech and language therapist, they will be advised to make a self-referral to their local service.

If they wish to take part, parents/guardians will contact the research team who will provide an electronic copy of the consent form. The consent form must be completed prior to commencement of any study activities. Given the age of the study population, 11‑36 months old, the children will not be provided with information about the research nor will their assent be sought.

#### Randomisation

Once informed consent has been given and baseline assessments have been completed, participants will be randomised by the clinical trial manager or other designated team member via Sortition® (a secure web-based clinical trial randomisation software developed by the University of Oxford) using block randomisation to receive standard care (Control) or standard care plus the intervention (Intervention) in a 1:1 ratio, stratified by site, to account for regional differences in standard care. Following randomisation, the parents/guardians will be contacted by the study team, who will explain their child’s study allocation and what will happen next.

#### Intervention group

Parents will be provided with a copy of the intervention manual (paper), a standard set of age-appropriate toys and books, a blank parent treatment diary and guidance on how to complete it and a study schedule of planned conversations with members or the study team and when to complete the assessments. The study team will remind parents of the importance to the study findings of not sharing the manual with other parents.

Parents will be asked to use the manual to support their child in developing their skills in responding to bids for shared attention. The parents will be asked to follow the manual stages and undertake 1 h of the intervention every week, split into several short sessions (3‑6 per week), in whichever way the parent chooses. Parents will be asked to record the date and duration of each session, how many toys they used and which stage they are working at, in the diary provided. Parents are asked to return electronically the diary weekly to the clinical trial manager.

Parents who do not complete the diary will be contacted by telephone or email at the end of the intervention period to remind them to return the diary, or to investigate the reasons for non-adherence. Two attempts will be made to contact parents, in order to respect their privacy and right to discontinue participation.

#### Control group

The children allocated to the control group will receive the standard care for this patient group. SLTs will record all contacts with the family for the duration of the study in terms of duration and activity (assessment, advice, intervention).

At the end of the 6-month follow-up period, they will be provided with the intervention manual, accompanying materials and corresponding SLT or member of the study team support.

#### Adherence to the intervention and contamination

Adherence to the intervention will be monitored by using a weekly diary. The Principal Investigators/Site Leads will phone the parents twice during the intervention period: in weeks 4 and 8 to check adherence, with a window of +/− 5 days. They will ask a standard set of questions including how closely parents are following the manual, how often they do the intervention and for how long. Having this information will allow us to have a log that can provide qualitative data as well as act as a metric of whether the intervention was acceptable to the parents and SLTs.

Any contamination that occurs between the intervention group and the control group will be measured at study entry. Parents will be asked whether they are familiar with the intervention materials, whether they have discussed the intervention with other parents or seen the manual and whether they may have carried out any activities as described in the manual. This will be part of a questionnaire that asks about previous interventions the children may have had. During the post-randomisation process, when parents are contacted by a member of the study team who will explain to them what the allocation means, they will be reminded that the materials are for their own use only and with their own child only and are not to be shared with other parents. In addition, the fact that the control group will be given access to the manual and accompanying materials at the end of the study should minimise contamination risks, as parents will be less likely to want to get hold of the manual via other parents.

### Data collection

All children in the intervention and in the control group will be assessed by an assessor blind to group allocation before randomisation/pre-intervention, immediately post intervention (3 months after) and at a 6-month follow-up, using the following instruments:Reading Communication Development Inventory [32], a parental checklist which assesses receptive and expressive language. This is also the primary outcome measure.Communication and Symbolic Behaviour Scale [33] which is a norm referenced instrument available as an online or paper questionnaire completed by parents/caregivers and assesses communicative functions, gestural communicative means, vocal communicative means, verbal communicative means, reciprocity, social-affective signalling and symbolic behaviour. This is the secondary outcome measure.Vineland Adaptive Behaviour Scale [34] assesses general cognitive and adaptive abilities and is completed by parents.Infant Toddler Quality of Life (ITQOL-SF47) [35] is a measure of infant quality of life.Adult Quality of Life Questionnaire [36]Hospital Anxiety and Depression Scale [37]

Participants will also complete a demographic questionnaire at baseline. All questionnaires will be completed by parents online or using paper copies posted to the participant (if that is what the parent wishes), with support from a member of the research team, if required.

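### Blinded outcome assessment is stated, but all six outcome instruments are parent-completed and parents know the allocation at both follow-up visits

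*Protocol article*

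**What the plan says.** On blinding, the Data collection section states: "All children in the intervention and in the control group will be assessed by an assessor blind to group allocation". The sentence covers all three time points and introduces the list of six instruments. The Methods paragraph of the Abstract repeats the claim, saying that the children's language and communication skills and the family health outcomes "will be assessed by a blinded assessor at baseline, post-intervention and 6 month follow-up".

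On who supplies the data, the same Data collection section describes the primary measure, the Reading CDI, as "a parental checklist which assesses receptive and expressive language". The Communication and Symbolic Behaviour Scale is "available as an online or paper questionnaire completed by parents/caregivers", and the Vineland "assesses general cognitive and adaptive abilities and is completed by parents". The section then covers every form at once: "All questionnaires will be completed by parents online or using paper copies posted to the participant", with help from the research team if needed. The Setting section agrees: "All assessments will be conducted remotely using either online or paper questionnaires, with support by telephone".

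On who knows the allocation, the Randomisation section has the study team contact parents after randomisation to explain the child's allocation. The section on adherence and contamination refers to the moment "when parents are contacted by a member of the study team who will explain to them what the allocation means". The Trial design and Intervention sections make the parent the person who delivers the programme at home.

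On use of the data, Data analysis and presentation plans a mixed model for the Reading CDI that yields adjusted means, treatment differences and 95% confidence intervals.

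**The concern.** Blinded outcome assessment protects a comparison only if the person whose judgement produces the score does not know the arm. Here that person is the parent. A parent who has spent 10 weeks working on shared attention, kept a weekly diary and taken adherence calls at weeks 4 and 8 may notice or credit more words than a parent in the control arm. Control parents also know their arm, and know that they will receive the materials later.

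Two things are at stake. First, the Reading CDI treatment differences could be taken for blind-assessed estimates. Second, the Aims and objectives and Outcomes sections say this study will show whether data collection methods need adjusting before a full trial. A mistaken statement that the primary measure is blind-assessed bears directly on that decision.

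**Working it through.** The plan gives no figure to reproduce, so the check sets the blinding statement against each instrument and each visit.

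**Step 1: respondent by instrument (Data collection, Setting).**

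| Instrument | Respondent | Described as rated by an assessor? |
|---|---|---|
| Reading CDI (primary) | Parent, stated for the instrument | No |
| Communication and Symbolic Behaviour Scale (secondary) | Parent or caregiver, stated for the instrument | No |
| Vineland | Parent, stated for the instrument | No |
| ITQOL-SF47 | Parent, by the general sentence on questionnaires | No |
| Adult Quality of Life Questionnaire | Parent, by the general sentence | No |
| Hospital Anxiety and Depression Scale | Parent, by the general sentence | No |

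Result: 6 of 6 are parent-completed and 0 of 6 are described as observed, tested or rated by an assessor. The Setting section leaves no room for a direct assessment of the child, because all assessments are remote questionnaires.

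**Step 2: respondent's knowledge of the allocation by visit (Randomisation, Adherence to the intervention and contamination).**

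- Baseline: completed before randomisation, so the parent cannot know the arm.
- Post-intervention: the parent has been told the arm.
- 6-month follow-up: the parent has been told the arm.

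Result: the respondent knows the allocation at 2 of 3 visits, and these are the two visits that supply the post-randomisation outcomes.

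**Step 3: what a blind staff member could still protect.** The article does not say what the assessor does with a form that the parent fills in. If that person sends, supports or scores forms without knowing the arm, prompting or scoring by arm is limited. The parent's answers remain unblinded.

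**Step 4: how reporting bias enters the planned estimate.** Let the mean reporting shift at a follow-up visit be b_I in the intervention arm and b_C in the control arm. For an unadjusted comparison:

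expected difference = true effect + (b_I − b_C)

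Sample size does not appear in this expression. Nor do the model's terms for baseline, site and age remove the bias term, because it arises after randomisation and differs by arm. The documents give no value for b_I or b_C, so none is put in.

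**The case against.** Several points on the other side are sound.

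- **Effectiveness is not determined in this study.** The Aims and objectives and Outcomes sections both say so. The success criteria in the Discussion concern recruitment, willingness to be randomised, therapist acceptability and delivery according to protocol. None uses a between-arm difference on the Reading CDI. This stands and limits the consequence. It does not remove it, because the treatment differences are still to be presented.
- **The respondent is disclosed.** The list that follows the blinding claim calls the primary measure a parental checklist, so a careful reader can see the problem. That is true, but it shows the contradiction rather than resolving it, and the Abstract does not name the respondent.
- **The full protocol may define staff roles.** The article condenses protocol version 1.4, which is not shown. Its silence on who administers or scores the forms, and on whether the person giving help is blind, is not a defect. The point here rests on a statement that the article itself contradicts.

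Three stronger readings are tempting but not supported:

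- A reader might infer that there is no protection at all. The documents do not exclude blind handling of the forms by staff, which would give limited protection.
- A reader might infer that every outcome and every visit is compromised. Baseline precedes allocation, and recruitment, retention and the therapist interviews do not come from these instruments.
- A reader might infer that the harm lies in the small sample, which is too imprecise to reveal a modest reporting shift. Step 4 shows why this is beside the point: the shift cannot be separated from the effect at any sample size, and the documents give no size for it.

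**Conclusion.** The statement is wrong as written. The outcome blinding claimed in the Abstract and in Data collection is not present at the post-intervention and 6-month visits for any of the six instruments. At most, staff handling is blind.

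The consequence is confined to two places: the Reading CDI treatment differences with their 95% confidence intervals, and the choice of data collection methods for the full trial. The feasibility conclusions are untouched. Nothing here shows that the standard deviation sought under Objective 6 is distorted; a constant shift within an arm would leave the within-arm standard deviation unchanged.

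The conclusion assumes that the general sentence on parent completion covers the three instruments whose respondent is not named separately, which is its plain meaning. It assumes nothing about the direction or size of reporting bias.

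**What to change.** 1. In the Abstract (Methods) and in Data collection, state that these outcomes are parent-reported: before allocation at baseline, and with knowledge of allocation at both follow-ups. A blanket label of unblinded parent report would be wrong for baseline.
2. Limit any blinding statement to what the blind staff member actually does, such as sending, supporting or scoring the forms.
3. In Data analysis and presentation, state beside the treatment differences that they come from unblinded parent report, are open to reporting bias, and do not support treating the Reading CDI as a blinded endpoint in the full trial.
4. Where existing staffing allows, have the blind assessor give any help with follow-up questionnaires.

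The first three items cost only wording. The fourth may be harder than it looks: the trial manager is part-time, may perform the randomisation and receives the diaries, and the principal investigators make the support calls. It is therefore conditional on staffing. Parent report can remain as the method. The downside is a less favourable risk-of-bias statement.
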